#### Primary Objective and End Points

We hypothesize that offering caregivers a supportive group intervention will empower them in their role by boosting their perceived support, strengthening their family function, and helping them to identify strategies to navigate the challenges of caregiving, ultimately benefiting both caregivers and patients.

The primary objective of this study is to evaluate the feasibility of the SUGRI intervention. The following parameters will be evaluated: recruitment, fidelity, adherence, acceptability, and safety (detailed in Table 1).

**Table 1 table1:** Progression criteria and feasibility parameters.

Study phase	Study	Aim and primary assessment	Data collection or assessment method	Progression criteria or predefined benchmarks
Exploratory phase	Systematic review	Aim: to identify and explore available evidence of outcome of supportive group interventions for caregivers to patients with a primary brain tumor Primary assessment: evidence from peer-reviewed literature	Data synthesis: guidance on the conduct of narrative synthesis in systematic reviews [31] Quality assessment: the Mixed Methods Appraisal Tool [32] PRISMAa guidelines [33]	Proceed to the development phase if: Review confirms a gap for group interventions of the target population Intervention already exists, reconsider scope or adapt intervention Review identifies sufficient evidence to inform group interventions to be positively evaluated
Development phase	PPI^b^ study	Aim: to involve caregivers in the design and development of a supportive group intervention targeted at caregivers to patients diagnosed with a glioblastoma and evaluate the PPI process Primary assessment: caregivers’ experiences and perceived meaningful impact of participation	Qualitative data: focus group interview guidelines by Krueger and Casey [34] Quantitative data: 22-item Patient Engagement in Research Scale [35,36]	Proceed to feasibility and evaluation phase if: A caregiver panel can be successfully established Intervention can be realistically developed in cooperation with the panel, integrating evidence and caregiver input
Feasibility and evaluation phase	Feasibility study	Aim: to test the feasibility of a supportive group intervention among caregivers to patients diagnosed with a glioblastoma Primary assessment: predefined feasibility parameters: Recruitment: is it feasible to recruit participants to the intervention? Fidelity: is the intervention provided as designed? Adherence: how feasible is it to ensure participants adhere to the intervention? Acceptability: what are the experiences and ratings of satisfaction with the intervention? Safety: is the intervention safe for participants?	Qualitative data: semistructured individual interviews with caregivers Quantitative data: patient- and caregiver-reported outcome Quantitative registration of recruitment rate Participants are offered the intervention Quantitative registration of intervention participation and participant feedback via study-specific questionnaires and interviews Participant feedback via study-specific questionnaires and interviews Adverse events from validated questionnaires and interviews	Proceed to development of a stepped care model if: All 5 feasibility parameters meet their predefined benchmarks Estimated recruitment ≥60%c Estimated fidelity 100%c Estimated adherence ≥70%c Estimated acceptability mean ≥4d Safety reported narrativelye

^a^PRISMA: Preferred Reporting Items for Systematic Reviews and Meta-Analyses.

^b^PPI: patient and public involvement.

^c^Recruitment rate, fidelity, and adherence are presented as estimates informed by other caregiver interventions and reported as percentages.

^d^Acceptability is defined as an average score of ≥4 on a 5-point Likert scale in a study-specific questionnaire. The questionnaire includes the item: “Overall, I found the caregiver program to be supportive,” rated from 1=not at all to 5=to a very great extent.

^e^Safety will be reported narratively based on individual postintervention evaluation interviews with caregivers, guided by the following question: “Have you experienced any concerns as a result of your participation that you did not have before?”

The proposed benchmarks for the 5 feasibility parameters have been guided by existing literature on caregiver interventions [38-41]. Predefined progression criteria, as proposed by the MRC framework, will be assessed through a feasibility study aligned with the evaluation design [24]. Moreover, progression criteria are used to guide the decision on whether to proceed to the next phase of the project [25]. Progression criteria for the 3 study phases—the exploratory phase, the development phase, and the feasibility and evaluation phase—are also presented in Table 1.

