Given the diverse nature of caregiver needs, shaped by demographic, course of the disease, and patient symptom burden, future research may benefit from moving beyond standardized approaches and explore the potential of multicomponent interventions [14,22]. Therefore, the MRC framework may provide an overall structured framework designed to guide this study. An intervention may be described as complex when it includes multiple components interacting with each other and allows for flexibility or tailoring [25]. The SUGRI intervention is planned to include 2 primary components: an informational element and a group-based element. Integration of these 2 components will be developed through a PPI process.

The updated MRC framework from 2021 includes 6 core elements to be addressed throughout the research process, one of which is engaging stakeholders [24]. Engagement of the stakeholders meaningfully at every stage of the research process is essential to develop interventions that positively impact health outcomes for patients and caregivers [24]. In the SUGRI project, we plan to establish a PPI collaboration with a panel of current and bereaved caregivers throughout the project. The MRC framework recommends involving stakeholders early in the research process [25]; however, out of respect for the caregivers’ time, we have chosen not to include them at the very beginning during the protocol stage. The protocol, while serving as the foundation for the project, is intentionally described in broad terms, as the detailed design of the intervention will be developed collaboratively with the caregiver panel. Given the poor prognosis of a GBM, we anticipate the panel to be dynamic, with caregivers leaving as patients enter end-of-life phases and new caregivers are invited to join. Most of the panel activities are scheduled to be online, as caregivers may have practical difficulties to schedule physical meetings due to their caregiver role.

The feasibility test of the SUGRI intervention aims to address caregivers’ supportive needs throughout the patient’s disease and treatment trajectory. Moreover, we anticipate the SUGRI intervention to inform how a tailored intervention can be both feasible and meaningful within the context of caregivers’ daily lives.

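### Fidelity is recorded as being offered the programme, which measures reach and does not show whether it was provided as designed

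*Protocol article*

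**What the plan says.** The Protocol article (Methods, Primary Objective and End Points) makes feasibility the primary objective and names five parameters: recruitment, fidelity, adherence, acceptability and safety. In the feasibility row of Table 1:

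- The question for fidelity is "Fidelity: is the intervention provided as designed".
- After two general lines on qualitative and quantitative data, the assessment column lists five entries. The first is "Quantitative registration of recruitment rate", the second is "Participants are offered the intervention" and the third is "Quantitative registration of intervention participation and participant feedback via study-specific questionnaires and interviews".
- The benchmark is "Estimated fidelity 100%c" (the last letter is a footnote mark). The footnote says that the result is reported as a percentage. It names no numerator, denominator or unit.
- Progression to a stepped care model requires that "All 5 feasibility parameters meet their predefined benchmarks".

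The Intervention section describes an informational element and a group element. Strengths and Limitations says that the intervention is not yet fully developed, and that its content, structure and timing are still uncertain.

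**The concern.** The question and the measure concern different things. A caregiver can be offered the programme while sessions are cancelled, the informational element is left out, or facilitators depart from the agreed content. The recorded value would be the same in every case.

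The consequence falls on the primary objective. A result of 100% would be reported as fidelity achieved and counted towards the decision to proceed, although delivery had not been measured. It would also be hard to interpret weak adherence or acceptability, because poor delivery could not be separated from a programme that was delivered well but did not suit its users.

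This is not a complaint that an article leaves operational detail to a fuller document. The article states a method, and that method does not answer the question beside it.

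**Working it through.** **Step 1. Which entry belongs to fidelity.** The text version of Table 1 has lost its cell layout, so the match rests on order:

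| Parameter | Assessment entry | Benchmark |
|---|---|---|
| Recruitment | registration of recruitment rate | ≥60% |
| Fidelity | participants offered the intervention | 100% |
| Adherence | registration of participation, with feedback | ≥70% |
| Acceptability | feedback by questionnaire and interview | mean ≥4 |
| Safety | adverse events from questionnaires and interviews | narrative |

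The order fits all five parameters in both columns, and no other entry describes fidelity.

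**Step 2. The benchmark as written.** The plan gives no calculation behind the 100%, so there is no figure to reproduce. The natural reading is

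fidelity = caregivers offered the programme / caregivers enrolled.

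If every enrolled caregiver is offered the programme, this is n/n = 100% for any n, whatever is then delivered. It falls short only if an enrolled caregiver is never offered it.

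**Step 3. The same 100% applied to delivery as designed.** Let n be the number of units (sessions or components) and p the probability that a unit is delivered as designed, with units independent. Then

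P(exactly 100%) = p^n.

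Neither n nor p is in the document. The only related figure is the sample size of about 30 in Feasibility and Evaluation Phase, which counts participants and not deliveries. All values below are therefore assumptions shown as a range.

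| Assumed units | p = 0.99 | p = 0.98 | p = 0.95 |
|---|---|---|---|
| 6 | 94.2% | 88.6% | 73.5% |
| 12 | 88.6% | 78.5% | 54.0% |
| 30 | 74.0% | 54.5% | 21.5% |

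For example, 0.98^12 = 0.785 and 0.98^30 = 0.545. One deviation among 30 units gives 29/30 = 96.7%, which misses the benchmark.

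**Step 4. What some tolerance would do.** As an example only, a threshold of 90% with 30 units means at least 27 of 30. By the exact binomial it is met with probability 93.9% at p = 0.95 and 0.9% at p = 0.70, so it separates good from poor delivery. With 6 units, 90% still means 6 of 6 (0.9 × 6 = 5.4, rounded up), so it gives no tolerance at all. A threshold can be chosen sensibly only once the number of units is known.

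**The case against.** **The offer may not be automatic.** Recruitment began in April 2025, while the intervention starts in August 2025 (Abstract) or autumn 2025 (Results). The Introduction gives a typical disease trajectory of 12 to 15 months. An enrolled caregiver may therefore never be offered some or all of the programme. This stands to the extent that about 100% is an expectation and not a certainty. A shortfall of that kind would still reflect timing or the course of the disease, and not whether delivery followed the design.

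**As a check on provision, 100% is coherent.** If the parameter means only that everyone is offered the programme, with uptake judged under adherence, requiring 100% is reasonable. That is fair, but it then answers a different question from the one in Table 1. A reader might also infer that the benchmark acts as an arbitrary veto. That arises only if the measure is changed and the threshold kept. The section also says that progression criteria guide the decision, and the footnote calls the percentages estimates.

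**Interviews may show how delivery went.** Qualitative Analysis says that interviews will help to evaluate specific elements of the intervention, so delivery is not wholly unexamined. But interviews do not supply the percentage that the benchmark requires, and the parameter-specific interview entries in Table 1 belong to other parameters.

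**Tailoring.** A reader might infer that 100% conflicts with the Discussion, which says that a complex intervention "allows for flexibility or tailoring". That is a general definition. Tailoring that the design permits is delivery as designed, so there is no contradiction.

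**Conclusion.** The point holds for the mismatch between question and measure. Being offered the programme is reach. For enrolled caregivers it will be about 100% in practice, so the fidelity benchmark adds almost nothing to the five-part progression decision and leaves its own question unanswered. This rests on the list order in the flattened table, which fits throughout, and on enrolled caregivers being offered the programme.

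A reader might go further and infer that 100% would fail a well-delivered programme. The figures do not support that. With an assumed 12 to 30 units at p = 0.98 to 0.99, the chance of passing is 55% to 89%, so passing is the likelier result throughout that range. The supported statement is narrower: once delivery is what is measured, any single deviation misses the benchmark. How often that happens depends on a number of units and a delivery rate that the document does not give. Clustering of deviations by session or facilitator would also change the percentages.

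This should be fixed. It affects one of five descriptive parameters of an intervention that is still being designed, and the remedy is cheap.

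**What to change.** In Table 1:

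1. Replace the fidelity assessment entry with planned components or sessions delivered as designed, divided by those planned. The facilitators record this on a short checklist at each session.
2. Freeze the component list when the caregiver panel finalises the design, and mark which parts may be tailored, so that permitted tailoring is not counted as a deviation.
3. Report the proportion offered the programme separately, labelled as reach.
4. With the number of units then known, reconsider the 100% benchmark and state a threshold with its reason before delivery data are seen. The documents give no basis for a particular value; the 90% in the working is only an example.

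The cost is a one-page checklist, a few minutes per session and edits to two cells of Table 1. No extra staff are needed, because the facilitators already run the sessions. The weakness is that facilitators report on their own delivery, which should be stated with the result. The checklist should be in place before sessions start if possible, because delivery records are hard to rebuild afterwards.

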The diagnosis of a GBM is usually preceded by symptoms such as an epileptic seizure, focal neurological deficits, or cognitive changes that may affect the patient’s functional status [2]. Patients often develop a complex symptom burden, including physical symptoms such as aphasia and hemiparesis and psychological symptoms such as cognitive deficits, anxiety, distress, and depression. The symptoms may change as tumor progresses [5-7]. The combination of a rapid onset of the disease, the intense disease and treatment trajectories, and the uncertainty of the future affect not only the individual but also those close to them who function as informal caregivers, a role that often demands great caring responsibilities [8,9]. The caregiver burden is described as multidimensional with components affecting caregivers physically, emotionally, socially, and economically [10]. Caregivers express being unprepared for the new role and report symptoms of anxiety and depression [4,9]. Additionally, social isolation is often a consequence of the caregiver role. Furthermore, the *invisibility* of the patients’ symptoms can lead to withdrawal of support from family and previous networks [4,11]. Caregivers emphasize the importance of meeting other caregivers in similar situations so that they can share experiences and recognize emotions or concerns in a peer-to-peer environment [12,13]. Peer support may represent an important access to information, advice, and practical help for caregivers and address caregivers’ individual needs of support [12,14,15]. It is often a struggle for caregivers to be separated from the patient, as they worry about risk of seizures or cognitive symptoms that necessitate constant supervision, a struggle that can be alleviated with support [16]. Online access to peer support and information may be valuable for caregivers. Such a tool is accessible and has the potential to ensure broad reach while remaining scalable at the national level. Moreover, online support aligns well with the recommendations of the International Council of Nurses, which indicate that digital health can address population needs, strengthen health systems, and remain feasible despite shortages in the health workforce [17].

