#### Measurements

Secondary outcomes are patient-reported outcome data completed by caregivers and patients at baseline, postintervention, and follow-up (Table 1). Caregivers will complete the following 3 questionnaires: the Caregiver Roles and Responsibilities Scale to assess broad life impacts for caregivers [42], the Iceland-Family Perceived Support Questionnaire to measure families’ perceived support from nurses and other health care professionals [43], and the Hospital Anxiety and Depression Scale to measure symptoms of anxiety and depression [44]. Patients will complete the following 3 questionnaires: the Functional Assessment of Cancer Therapy-Brain to assess the patients’ health-related quality of life [45]; the MD Anderson Symptom Inventory-Brain Tumor Module to measure patients’ symptom prevalence, intensity, and interference with the daily life [46]; and Hospital Anxiety and Depression Scale [44]. The questionnaires and time assessment are presented in Table 2 and will be collected electronically using Research Electronic Data Capture (REDCap; Vanderbilt University). Demographic data of the participants will be completed at baseline, and information on patient histology will be obtained from the patient’s medical journal and stored in REDCap.

**Table 2 table2:** Measurement tools and assessment time points for the feasibility study.

Outcome measurement tools			Caregiver							Patient			
			T0^a^		T1^b^		T2^c^		T0			T1	T2

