### Ethical Considerations

The study adheres to the ethical standards of the institutional and national research committee and complies with the Declaration of Helsinki. The study was approved by the ethical committee of the Capital Region of Denmark (F‑24004933) and registered with the Danish Data Protection Agency (Jr. P‑2022‑739). No compensation is provided for participation. Potential ethical risks include breaches of privacy or integrity, while other types of harm are considered unlikely. Study participants as well as future patients and caregivers may benefit from the study. Measures will be taken to protect integrity. Participants will be enrolled based on oral and written informed consent, which can be withdrawn at any time. All participants will provide written informed consent before enrollment and will be informed about procedures related to confidentiality, safeguarding, and support throughout the intervention. Clear rules for confidentiality will be established at the beginning of the online group sessions, including reminders to not share identifiable information outside the group. To ensure participant well-being, facilitators will be attentive to recognizing signs of emotional distress during the sessions. If a participant appears overwhelmed, they will be offered a one-on-one follow-up conversation and, if necessary, referred to appropriate support services.

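### The guiding safety question covers only new concerns, and footnote e leaves out the questionnaires that Table 1 names, so worsening of existing distress can be missed

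*Protocol article*

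**What the plan says.** Safety is one of five primary feasibility parameters (Primary Objective and End Points, Table 1). Progression to a stepped care model requires all five to meet their benchmarks. The benchmark column for safety says only that it is reported narratively.

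Two places in Table 1 say where the safety information comes from:

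- The assessment column: "Adverse events from validated questionnaires and interviews".
- Footnote e: "Safety will be reported narratively based on individual postintervention evaluation interviews with caregivers, guided by the following question", followed by "Have you experienced any concerns as a result of your participation that you did not have before".

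Three other parts of the article bear on the point:

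- On the population, the Introduction states: "Caregivers express being unprepared for the new role and report symptoms of anxiety and depression".
- Under Measurements, caregivers complete the "Hospital Anxiety and Depression Scale to measure symptoms of anxiety and depression". The questionnaires are "completed by caregivers and patients at baseline, postintervention, and follow-up" and are classed as secondary outcomes.
- Under Ethical Considerations, "facilitators will be attentive to recognizing signs of emotional distress during the sessions", and if a participant appears overwhelmed, "they will be offered a one-on-one follow-up conversation and, if necessary, referred to appropriate support services".

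**The concern.** A safety question should be able to pick up the harm that is most plausible in the population studied. These caregivers enter the programme with anxiety, depressive symptoms and worry about the future. In a peer group, a likely harm is that an existing fear grows, for instance after hearing how other families have fared. A question limited to concerns the caregiver did not have before is poorly suited to detecting that.

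The study does collect something better suited, a validated before-and-after measure of anxiety and depression, and one cell of Table 1 appears to count on it. The footnote that defines the safety report does not.

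What is at stake is a primary parameter that feeds the progression decision. If the information behind it is insensitive to worsening, the narrative leans towards no harm. This is separate from the lack of a safety benchmark: adding a benchmark would not make the question more sensitive.

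**Working it through.** The protocol gives no safety rate or threshold, so there is no figure to reproduce. The check sets the texts side by side.

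**1. What the question covers.** As worded, it sets two conditions: the concern is new, and the caregiver sees it as a result of taking part.

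| Experience during the programme | Attributed to participation | Covered by the literal wording |
|---|---|---|
| New concern | Yes | Yes |
| New concern | No | No |
| Existing concern became worse | Yes | No |
| Existing concern became worse | No | No |

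The third row matters most. A caregiver who believes the group made an existing fear worse could truthfully answer no.

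**2. Whether that row is likely to be occupied.** The Introduction says the population already reports anxiety and depression. It gives no proportion, so the number of caregivers affected cannot be estimated.

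**3. Whether another source fills the gap.** The Table 1 cell names validated questionnaires as a source of adverse events. Table 2 schedules the caregiver HADS at T0 (baseline), T1 (week 12) and T2 (week 18), so the data to see individual worsening will exist. Three things stop them from reaching the safety report as the text stands:

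- Footnote e names interviews alone as the basis.
- The article does not say which questionnaire result is an adverse event.
- The Statistical Analysis section plans descriptive statistics and mean change from baseline, possibly by a linear mixed model, and calls the secondary analyses exploratory. A mean change can be nil or favourable while a few caregivers become clearly worse.

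**4. Distress seen in sessions.** Ethical Considerations provides for recognising distress, offering a conversation and referring. Footnote e does not mention these events, and the ethics text does not mention the safety parameter. The article is silent on whether they are recorded.

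**5. Timing.** Table 2 places the interview at T1 only, and Measurements describes it as held with the participating caregivers after the intervention. The article does not say whether caregivers who leave early are asked.

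**The case against.** The strongest counter-argument is that the protocol already measures worsening. The Table 1 cell names validated questionnaires, the HADS is repeated in caregivers, and change from baseline is analysed. In addition, the question guides a semistructured interview that is transcribed and analysed thematically. It is not a yes/no item, and an interviewer may probe. This is also a condensed article on a feasibility study of about 30 caregivers, and its full protocol may hold an interview guide and a recording procedure.

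Much of this stands, and it rules out several stronger readings that a reader might infer:

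- **That worsening is not treated as a harm.** The questionnaire cell contradicts this.
- **That distress handled in sessions is not counted.** The article does not say so; it only fails to link those events to safety.
- **That a particular harm rate would be missed.** Safety is narrative, and the documents give no rate. Nor does the adherence benchmark of at least 70% help, because a caregiver who does not adhere has not necessarily withdrawn or gone without an interview.
- **That a breach of privacy would escape the question.** A breach the caregiver knows of would be a new concern arising from participation, which is what the question asks about.

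What the objection does not remove is the printed wording. Footnote e fixes both the source and the guiding question. The article does not commit to any probe about worsening, and group means are not a safety listing. The questionnaire cell therefore leaves a mismatch with the footnote that needs resolving.

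**Conclusion.** The point holds in a limited form. The guiding question is restricted to new concerns attributed to participation, in a population described as already distressed, so it can miss worsening. The questionnaire data that could make up for this are named in one cell of Table 1, left out of footnote e, and analysed only at group level as exploratory outcomes.

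The direction of the effect is towards under-detecting harm in one of five primary feasibility parameters. Its size cannot be stated, because the documents give neither the frequency of distress at baseline nor an expected rate of worsening.

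The conclusion assumes that footnote e is followed as printed and that an interview guide not shown does not already ask about worsening. For in-session distress and early leavers, the finding is only that the safety text does not mention them. The change is worth making because it is specific and costs very little.

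**What to change.** 1. **Reword the guiding question** to ask whether any concern or distress has arisen or become worse during the programme. Whether the caregiver thinks the programme caused it can be a follow-up question.
2. **Reconcile footnote e with the Table 1 safety cell.** Name the interviews and the questionnaires as joint sources, and report individual caregiver worsening on the HADS from baseline to T1 and T2 under safety. The investigators should state in advance what they will count as worsening; no threshold is proposed here.
3. **Put the question also to caregivers who leave early**, at the time they leave.
4. **Report under safety the one-on-one conversations and referrals** that facilitators already make. If a log exists in the full protocol, footnote e need only refer to it.

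The cost is one reworded interview question, a revised footnote, a listing from HADS data already being collected, a short contact with early leavers, and a simple session log. None of this alters how distressed participants are managed. The small downside is that more events will be reported, and some will reflect the course of the patient's disease and not the programme. The narrative should say so.
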